### Power and sample size

This study is powered to estimate the efficacy of PrOMOTE compared to TAU on abstinence from smoking at EOT. Investigations on the efficacy of varenicline note increases in 7-day PPA in active varenicline treatment arms as compared to placebo (Week 12: 50.3% vs. 21.2%; Δ = 29.1% and 50.3% vs. 20.8%; Δ = 29.5%).[64, 65] Similarly, Ashare and colleagues completed a trial of varenicline compared to placebo in PWH and noted that varenicline was superior to placebo at the close of treatment (PPA: 28.1% vs. 12.1%; Δ = 16.0%).[26] Further, dual NRT (long term patch + *ad lib* NRT) was similarly efficacious for abstinence at 6 months post quit as varenicline [dual NRT: abstinent = 36.5% (95% Confidence Interval [CI] = 28–45) and varenicline abstinent = 33.2% [29–38]].[13] Sample size will be based on a conservative estimate of the effect sizes provided above (Δ = 17%). Thus, a TAU abstinence rate of 15% is anticipated with a PrOMOTE abstinence rate of 32% at EOT. To detect this clinically-relevant effect size with 80% power and a type 1 error rate of 5%, n = 95 participants will be randomized to each of the two treatment assignments. Continuous abstinence from study Week 9 through 12 (4 weeks) will also be assessed as a primary efficacy outcome. Estimates on the efficacy of varenicline as compared to placebo note significant increases in 4-week end of study abstinence in the active varenicline treatment arms as compared to placebo at the close of study treatment (Week 12: 44.0% vs. 17.7%[64]; Δ = 26.3% and 43.9% vs. 17.6%; Δ = 26.3%[65]). Based on preliminary data, TAU continuous abstinence rate of 10% is anticipated with a PrOMOTE abstinence rate of 25% at the Week 12 (Δ = 15%). To detect this effect size with 80% power and a type 1 error rate of 5%, n = 97 participants will be randomized to each of the two treatment assignments. The study design will employ remote intervention delivery and follow-up assessments reducing participant burden and enhancing data collection. This, combined with the flexibility of medication management using PrOMOTE, a moderate to low attrition rate at EOT (15%) is anticipated. Thus, n = 115 participants randomized to each study treatment assignment (n = 230 total) will provide adequate power at a 5% type 1 error rate to detect the anticipated effect sizes.

### Data safety monitoring

Data will be collected on a secure, password-protected, electronic Web-based form and sent to a secure database in REDCap. Only research staff have access to the database. Participants will be assigned a study ID to protect confidentiality. The principal investigator (PI) will be responsible for monitoring the data, assuring protocol compliance, and conducting the safety reviews. A Data Safety Monitoring Board (DSMB) has been convened and consists of 3 investigators and 1 statistician who are independent of the proposed trial and experienced in various aspects of the conduct of clinical trials for tobacco treatment and/or clinical care for PWH. The PI will be responsible for monitoring the data, assuring protocol compliance, and compiling the data for safety reviews. Every 6 months the DSMB will review: (1) recruitment, retention, and follow-up rates for the study and compare them to target rates, (2) occurrence of all adverse events delineated by severity grading and causal relationship to study, (3) rates of recruitment of women and minorities with respect to targets, and (4) any other data that will help in the assessment of the clinical trial. These reports will be generated by the data manager every 6 months, and reviewed by the PI prior to their submission to the DSMB. During the review process, the DSMB, PI, and study staff will meet, minutes will be kept, the report will be reviewed, and the DSMB will vote on whether the study should: (1) continue with recruitment unchanged; (2) continue with a protocol amendment; (3) stop the study pending further investigation. If protocol modification or study suspension is needed, the PI will immediately inform the institutional review board (IRB). DSMB comments will be documented and forwarded to the IRB at the time of the annual review and reapproval; study-related serious adverse events and unanticipated problems will be reported in real time to the local IRB, the National Cancer Institute, and other regulatory entities as required.

### Planned analyses

Baseline clinical and demographic characteristics will be collected and preliminary analyses will examine significant correlates of study outcomes. Characteristics found to be significantly associated with primary outcome measures will be included as covariates in the initial stages of adjusted model development. Exploratory analysis of the modifying effects of participant sex on study outcomes will be assessed through main effects and the interaction between sex and study treatment assignment. Where significant interactions are found, sex-stratified analyses will be conducted to determine what role sex plays in the effect of varenicline on smoking outcomes in PWH. All statistical analyses will be conducted using the intent-to-treat (ITT) principal and will be completed using SAS v9.4 software.[66].

Clinical efficacy hypothesis: The primary study outcome of interest are the efficacy of PrOMOTE as compared to TAU in achieving biologically confirmed 7-day PPA and 4-week CA from cigarettes at EOT in PWH. To test these hypothesis, logistic regression models utilizing the sandwich variance estimate[67] will be developed. An ITT analysis will be utilized assuming participants that were lost to follow-up and those who withdrew from the study are smoking. Additionally, a completer analysis (participants who complete the Week 12 assessment) will be compared to the ITT results.

Additionally, participants will report all treatment emergent 24-hour quit attempts during study treatment (through Week 12). A Poisson distribution will be assumed with a logarithm link function to assess the effects of PrOMOTE on the number of quit attempts made as compared to TAU. Over-dispersion due to a wider than expected distribution in discrete count models (from heterogeneity) can have a significant impact on parameter inference, thus when detected, a negative binomial (NB) distribution will be specified.

Further, changes in CD4 and CD8 cell counts and the proportion of participants with detectable vs. undetectable HIV-1 RNA viral load will be examined from study baseline to Week 12 and Week 24, and participants who do and do not achieve abstinence will be compared at each timepoint. Generalized linear mixed effects regression models with appropriate distributions will be utilized to make comparisons. Model covariates will include baseline characteristics that were associated with follow-up abstinence.

Secondary examination of implementation outcomes: Descriptive statistics will be used to characterize implementation outcomes at the participant and provider level on reach (number and type of participants randomized, the number of contacts made, answered, and completed), provider fidelity (number of contacts completed and number of prescriptions written), participant adherence (number of prescriptions filled), medication adherence (assessed as both a continuous variable of percentage of prescribed medication taken as well as binary yes/no ≥ 80% adherence achieved), and acceptability (average score on the AIM Survey). Implementation outcomes for PrOMOTE will be characterized, and contrasts will also be performed between randomized treatment study arms (PrOMOTE vs. TAU). Continuous and ordinal outcomes will be compared using a Wilcoxon Rank-Sum test statistic while categorical outcomes will be compared using a Pearson Chi-Square test statistic.

Qualitative analysis: Transcriptions of digital recordings of participant and provider interviews will be analyzed to identify key barriers and facilitators to implementation processes and outcomes using content analysis[68] with NVivo software[69] to identify, categorize, and contextualize theme patterns. Two independent coders will read and reread transcripts for all qualitative analyses, outlining and organizing key themes and sub-themes. Discrepancies will be discussed in team quality assurance meetings to develop consensus.

Data synthesis: After completing qualitative and quantitative data analyses independently, results will be synthesized to relate quantitative findings from surveys and tracking logs with qualitative data for the purpose of analysis and data triangulation.[70] Themes identified in qualitative data will be supplemented by patterns identified in quantitative findings to characterize provider and participant impressions.

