### Randomization

Participants will be randomized to a treatment assignment (treatment as usual [TAU] or Proactive Outreach with Medication Opt-out for Tobacco Treatment Engagement [PrOMOTE]) in a 1:1 allocation. Randomization will be done using a stratified random block design and will be stratified across biological sex at birth and motivation to quit (motivation ladder; low: 0–7 vs. high: 8–10). Participants randomized to PrOMOTE will be scheduled to see the Tobacco Treatment Program clinical pharmacist. Those randomized to TAU will follow traditional clinic pathways for receiving tobacco treatment in the infectious diseases (ID) outpatient clinic.

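### Covariates are chosen by significance against the trial's own primary outcomes, and the text does not say which model is primary or fix the randomisation strata in it

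*Protocol article*

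**What the plan says.** Under Planned analyses, the protocol article first looks for baseline correlates of the study outcomes and then states: "Characteristics found to be significantly associated with primary outcome measures will be included as covariates in the initial stages of adjusted model development". The efficacy paragraph of the same section tests the two abstinence outcomes with "logistic regression models utilizing the sandwich variance estimate" and names no covariates. Quit attempts get a Poisson model, or a negative binomial one if over-dispersion is found, again without named covariates.

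Under Randomization, allocation "will be stratified across biological sex at birth and motivation to quit", the latter split at 0–7 versus 8–10. In Planned analyses, sex returns only as an exploratory effect modifier. Motivation is not mentioned there.

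Under Power and sample size, the trial is sized on two simple proportions for each abstinence outcome, and no covariate adjustment is assumed.

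**The concern.** This is a rule that the document states, not a detail left to an analysis plan that is not shown. It screens baseline variables on the outcomes of the trial being analysed. Three things remain open:

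- which variables are screened, and at what level;
- what follows the initial stage of model development;
- whether the resulting model or the unadjusted one is primary.

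The abstract lists three primary outcomes, and each could end up with a different covariate set. A logistic odds ratio is conditional on its covariates, so the quantity being estimated would also change with the selection, and the reported interval would not reflect the selection step. A reader could not tell whether the reported model was the only one tried. The strata were thought important enough to balance on, yet the stated analysis gives them no guaranteed place.

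**Working it through.** **1. The plan's own figures.** The inputs are in Power and sample size: "a TAU abstinence rate of 15% is anticipated with a PrOMOTE abstinence rate of 32% at EOT", "TAU continuous abstinence rate of 10% is anticipated with a PrOMOTE abstinence rate of 25% at the Week 12", 80% power, 5% type I error (taken as two-sided, which is the reading that reproduces the figures), and "a moderate to low attrition rate at EOT (15%) is anticipated".

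n per arm = (1.960 + 0.842)² × [p₁(1−p₁) + p₂(1−p₂)] / (p₂−p₁)²

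- Point prevalence (PPA): 7.849 × (0.1275 + 0.2176) / 0.0289 = 93.7, so 94 (plan: 95).
- Continuous abstinence (CA): 7.849 × (0.0900 + 0.1875) / 0.0225 = 96.8, so 97 (plan: 97).
- Attrition: 97 / 0.85 = 114.1, so 115 per arm (plan: 115).

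The sample size stands, and this point does not change it. At 115 per arm the pooled-variance test has 86.5% power (PPA) and 85.4% (CA).

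**2. Simulating the rule.** The set-up was n = 230, 1:1 allocation in blocks of 4 within sex × motivation, logistic regression with sandwich variance, and 3,000 replicates. There were 14 candidates: the two strata and 12 others. The screen was p<0.05, applied once. The documents give no prognostic strengths, so three sets are assumed, as odds ratios for motivation / sex / one further covariate per SD: none (1/1/1), moderate (2/1.3/1.5) and strong (4/1.5/2). Stratum shares (40% one sex, 50% high motivation), block size, threshold and number of candidates are also assumptions. Monte Carlo error is about 0.4 points for type I error and 0.6 for power.

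Power, %, for none / moderate / strong:

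| Model | PPA 15% vs 32% | CA 10% vs 25% |
|---|---|---|
| Unadjusted | 87.1 / 87.3 / 87.0 | 85.6 / 86.2 / 87.0 |
| Strata fixed | 87.3 / 88.0 / 88.7 | 85.7 / 86.7 / 88.5 |
| Selected at p<0.05 | 86.7 / 87.0 / 89.2 | 84.9 / 86.5 / 89.3 |
| Strata + one prespecified covariate | 87.1 / 88.1 / 89.8 | 85.5 / 87.2 / 90.0 |

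Fixing the strata gains 0.1 to 1.7 points over no adjustment. The selection rule loses at most 88.1 − 87.0 = 1.1 points against a prespecified model, and in the strong scenario it beats strata alone.

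**3. Type I error.** Over both outcomes and all three scenarios, the null rejection rate is 3.8–5.1% unadjusted, 4.3–5.2% with strata and 3.9–5.3% with the single selection rule. If the analyst may instead take the best of four models (unadjusted, or selected at p<0.05, 0.10 or 0.20), it is 6.1%, 6.3% and 6.2% for PPA in the three scenarios.

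**4. Stability of the model.** With a true odds ratio of 2, motivation passes the screen in 44% (PPA, null), 52% (PPA, planned effect), 33% (CA, null) and 44% (CA, planned effect) of trials. With no prognostic variable at all, about 14 × 0.05 = 0.7 variables are still selected on average.

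**5. How far the odds ratio moves.** The planned PPA rates give an unadjusted odds ratio of (0.32/0.68) / (0.15/0.85) = 2.67. Suppose half the participants are highly motivated, with motivation odds ratio k and a constant treatment odds ratio. The odds o in the low stratum then solve ½·o/(1+o) + ½·ko/(1+ko) = p.

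- k = 2: o = 0.1197 (TAU) and 0.3256 (PrOMOTE), so the conditional odds ratio is 2.72.
- k = 4: o = 0.0748 and 0.2154, so it is 2.88.

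The target therefore changes with the selected set, modestly for this one factor.

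**The case against.** The strongest defence is that the screening rule concerns adjusted models only. The efficacy paragraph names no covariates and the trial is sized on unadjusted proportions, so an unadjusted primary test with supportive adjusted models is a fair reading. That stands as a possible reading, and it is why the point is that the text does not say which model is primary, not that the primary estimate is certainly data-driven.

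Second, a reader might infer that the rule wastes power. The simulation of the rule does not support this: the loss is about 1 point or less. Counting the 15% lost as smokers lowers the PPA rates to 0.85 × 15% = 12.75% and 0.85 × 32% = 27.2%. A separate run at these rates (2,000 replicates, p<0.05 screen, 10 noise candidates) compared the rule with a fixed model of sex, motivation and nicotine dependence (FTND). Power was 78.8 vs 79.9%, 80.9 vs 81.7% and 82.9 vs 83.5%, differences within Monte Carlo error of about 0.9 points per estimate. Larger gains, such as 78.7% to 83.5%, arise only when an unadjusted model is compared with one that includes FTND at an assumed odds ratio of 0.5 per SD. They come mostly from FTND, not from the strata.

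Third, a reader might infer that the strata enter only if significant. The text says that significant characteristics will be included. It does not say that nothing else will be, and an analysis plan that is not shown may fix them. This part is therefore weaker than the selection rule. It is still right that the stated analysis gives the strata no fixed place.

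**Conclusion.** The point holds as a lack of prespecification. The protocol article states an outcome-driven selection rule with no threshold or candidate list, leaves open whether the adjusted or unadjusted model is primary, and does not fix the strata. The chosen model depends on chance and can differ across the three primary outcomes. The inflation to about 6% is conditional on choosing among models after seeing results. The document does not say that this will happen, but its wording does not prevent it. The text does not support a claim that the rule, applied once, invalidates the test or materially reduces power. The sizes rest on the assumed prognostic strengths and screening set-up given with the check. This should be corrected, but the sample size is not affected.

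**What to change.** Replace the selection sentence with one primary model per outcome, named in advance: logistic for PPA and CA, Poisson or negative binomial for 24-hour quit attempts. Each contains treatment, sex at birth and motivation stratum (0–7 vs 8–10). Baseline FTND may be added as a prespecified prognostic covariate, in which case it should be in all three. State that this model carries the primary inference, and that unadjusted and significance-selected models are supportive only. A marginal risk difference beside the odds ratio would match the scale on which the trial was sized, but it is an optional addition, not a correction.

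The cost is one paragraph. Both strata are known at randomisation and FTND is already a baseline measure. If an analysis plan already fixes the model, this paragraph should be brought into line with it. The change should be made before outcome data are examined by arm.

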### Procedures

Participants who consent to participation and are randomized will complete baseline assessments and a blood draw for baseline measurements of CD4/CD8 cell counts and HIV-1 RNA (viral load). Participants will be compensated for completion of the baseline interview; transportation and testing will be paid by the study.

Treatment as usual (TAU)TAU participants will follow traditional clinic pathways for receiving tobacco treatment in the HIV outpatient clinic. This typically consists of patients seeing the ID clinical pharmacist (PharmD) for medication management (ART and any other medications to treat comorbidities). The clinical pharmacist can prescribe pharmacotherapy if a patient is a current smoker and is interested in quitting. Thus, the TAU approach is conducted in an opt-in fashion. However, all participants randomized to TAU will have the opportunity to access smoking cessation pharmacotherapy from the clinical pharmacist if they choose to opt-in.

Proactive outreach with medication opt-out for Tobacco Treatment Engagement (PrOMOTE): The treatment will consist of a proactive, opt-out, pharmacist-led smoking cessation counseling and pharmacotherapy intervention. All participants who are randomized to receive the PrOMOTE intervention will be proactively scheduled for a virtual (HIPAA-compliant video conferencing or telephone) session with the clinical pharmacist (PharmD). The clinical pharmacist will assess their smoking status, conduct a motivational interview (described below), and arrange a prescription for pharmacotherapy (described below). They will schedule the participants for two additional sessions (approximately every 4 weeks) to assess medication adherence, potential side effects, and provide additional cessation counseling or relapse prevention counseling as needed. The clinical pharmacist will also create a note in the participant’s electronic medical record documenting the clinical encounter, counseling content checklist, the medications that were prescribed and mailed, adverse events review, and updates about the participant’s smoking status.

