*Brief counseling*: The clinical pharmacist will conduct a brief motivational interview and counseling session[13] that focuses on the benefits of quitting smoking, committing to a quit attempt, cigarette tracking to identify smoking cues, and behavioral strategies to manage cravings and stress. The counseling provided by the clinical pharmacist will be based on practical counseling, which is a cognitive-behavioral, evidence-based, smoking cessation treatment modality,[13] and motivational interviewing.[42] The counseling session will last approximately 30 min.

*Pharmacotherapy*: Based on the recent American Thoracic Society Clinical Practice Guidelines, preference will be given to prescribing varenicline over NRT.[12] Participants will be informed that they medically qualify for a 12-week prescription of varenicline. If they opt-out of varenicline use (or cannot take it due to medical comorbidities such as renal disease), the clinical pharmacist will offer dual NRT (nicotine patches and lozenges) or bupropion. If the participant opts out of any medication use, the pharmacist will conduct a brief motivational interview to encourage the use of smoking cessation pharmacotherapy. If the participant still elects to opt out, the clinical pharmacist will offer follow-up behavioral counseling. The medication opt-out language from the clinical pharmacist will be consistent for each participant and scripted: *“What I would like to do is prescribe you varenicline to help you quit smoking. I have reviewed your chart and varenicline is safe to use with your other medications and has been shown to reduce cravings to smoke. I reviewed your prescription coverage and this medication will be $__. If I can verify your address, I will mail this directly to you.”*

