## Discussion

This is the first study to test an opt-out, proactive tobacco treatment delivery approach with a focus on pharmacotherapy and behavioral support. The intervention is low-cost, has the potential to be highly scalable, and could be translatable to other ambulatory HIV clinic settings. This study will add to the literature on varenicline and NRT efficacy in PWH. Although varenicline and NRT have been independently shown to be effective for smoking cessation, there are very few studies evaluating these pharmacotherapies in PWH. Whether these approaches will improve quit rates for PWH in an ambulatory clinical setting is an empirical question. Of note, this trial can be conducted completely remotely using rigorous methods that have been well-established. An exploratory assessment of mediators and moderators of smoking cessation outcomes (i.e., nicotine dependence, medication adherence) is also an important feature of this study as these variables are understudied in PWH. We will examine implementation experiences concurrent with the trial to advance future dissemination of PrOMOTE.

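### The sex-stratified analyses are said to address the effect of varenicline, but the trial randomises and models PrOMOTE against TAU

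*Protocol article*

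**What the plan says.** All references are to the protocol article.

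- **Randomization:** equal allocation to PrOMOTE or TAU, with the blocks "stratified across biological sex at birth and motivation to quit".
- **Procedures, PrOMOTE arm:** a "proactive, opt-out, pharmacist-led smoking cessation counseling and pharmacotherapy intervention", with a first pharmacist session and two further ones. Varenicline is preferred. For participants who decline it or cannot take it, "the clinical pharmacist will offer dual NRT (nicotine patches and lozenges) or bupropion". Participants may also refuse all medication and still be offered behavioural counselling. Adding NRT, and switching between varenicline and dual NRT, are allowed.
- **Procedures, TAU arm:** "all participants randomized to TAU will have the opportunity to access smoking cessation pharmacotherapy from the clinical pharmacist if they choose to opt-in".
- **Planned analyses:** effect modification by sex is exploratory and is assessed through main effects and "the interaction between sex and study treatment assignment". All analyses follow intention to treat. If the interaction is significant, "sex-stratified analyses will be conducted to determine what role sex plays in the effect of varenicline on smoking outcomes in PWH".
- **Power and sample size:** power is claimed only for PrOMOTE against TAU overall. The split by sex is not given.

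**The concern.** The model and its stated purpose refer to different effects. The model contrasts randomised arms. The purpose clause speaks of a drug that is not randomised, that some PrOMOTE participants will not take, and that is only one part of what differs between the arms.

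If the abstinence difference between arms were larger in one sex, several explanations would be open: differential response to outreach or counselling, a different opt-out rate, a different choice among drugs, different adherence, or different uptake of cessation drugs in TAU. Nothing in the planned comparison separates these from a sex difference in the action of varenicline. A report written to the stated aim would credit the drug with a finding that belongs to the delivery strategy.

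A second, smaller point concerns the condition on the stratified analyses. Running them only after a significant interaction has a cost when that test has low power: the estimates are usually not produced, and those that are produced come from samples in which the sex difference happened to look large.

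**Working it through.** **1. Which effect is estimated**

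| Element | What the article fixes |
|---|---|
| Randomised contrast | PrOMOTE against TAU |
| Content of PrOMOTE | outreach, counselling, opt-out offer; varenicline, dual NRT, bupropion or no drug |
| Drug access in TAU | cessation pharmacotherapy by opting in |
| Analysis principle | intention to treat |
| Term tested | sex by study assignment |
| Stated aim of the strata | role of sex in the effect of varenicline |

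The first five rows define the effect of PrOMOTE compared with TAU, by sex. Only the last row departs from it. The efficacy hypothesis in the same section and the power section both name PrOMOTE against TAU, so the departure is confined to one clause.

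**2. The plan's own sample size**

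Inputs (Power and sample size): 15% against 32% for 7-day point prevalence; 10% against 25% for continuous abstinence; 80% power; 5% type 1 error (taken as two-sided); 15% attrition.

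Arcsine formula: n = 2 × [(1.960 + 0.842) / h]², with h = 2·asin√p₂ − 2·asin√p₁.

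- Point prevalence: h = 0.4071, n = 94.7, so 95 (stated 95).
- Continuous abstinence: h = 0.4037, n = 96.3, so 97 (stated 97).
- Attrition: 97 / 0.85 = 114.1, so 115 per arm (stated 115).

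The plan's figures reproduce.

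**3. Power of the sex-by-arm interaction on the planned logistic scale**

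Assumptions that the article does not supply: 20% to 50% women, and the full planned effect in men (15% against 32%) with none in women (15% against 15%). All 115 per arm are counted, because missing participants are analysed as smoking.

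- Difference in log odds ratios: ln[(0.32/0.68) / (0.15/0.85)] = ln 2.667 = 0.981.
- Variance in men: 1/(n_m × 0.15 × 0.85) + 1/(n_m × 0.32 × 0.68).
- Variance in women: 2/(n_w × 0.15 × 0.85).
- SE = square root of the sum; power = Φ(0.981/SE − 1.960) + Φ(−0.981/SE − 1.960).

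| Women | n_w, n_m per arm | Variance women + men | SE | 0.981/SE | Power |
|---|---|---|---|---|---|
| 20% | 23, 92 | 0.682 + 0.135 | 0.904 | 1.085 | 19% |
| 30% | 34.5, 80.5 | 0.455 + 0.155 | 0.781 | 1.257 | 24% |
| 50% | 57.5, 57.5 | 0.273 + 0.216 | 0.699 | 1.402 | 29% |

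With 97 per arm the range is 17% to 25%. With the effect in women only, at 115 per arm, it is 21% to 29%. About 459 per arm (50% women) to 648 per arm (25% women) would be needed for 80% power in the tabulated scenario.

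**4. What the significance condition does to the estimates**

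To pass at the two-sided 5% level (assumed; the article sets no level for the interaction), the observed ratio of odds ratios must be at least exp(1.960 × SE): 5.9 at 20% women, 4.6 at 30% and 3.9 at 50%. The assumed true ratio is 2.67. Under the normal approximation, the mean estimate among significant results, on the log scale, is about 2.3, 2.0 and 1.8 times the true value respectively.

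**The case against.** The best defence is that the operative instructions are sound. The interaction is with study assignment, the analysis is by intention to treat, and an analyst who follows them will estimate PrOMOTE against TAU by sex. The slip sits in a purpose clause. This is true, and it limits the damage: no model, population or sample size is wrong. It does not remove the point, because the clause states what will be concluded, and an exploratory analysis must still name the effect it estimates.

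Three stronger readings are tempting, and the article does not support them.

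- **That the whole sex analysis appears only if significant.** The main effect of sex and the interaction are assessed unconditionally. Only the stratified follow-up is conditional, and no reporting rule is stated. A model with arm, sex and their product also contains the arm effect in each sex.
- **That low interaction power is itself an error.** The analysis is labelled exploratory and no power is claimed for it. Testing an interaction before looking within strata is a common guard against over-reading subgroups. The power figures above only show why the condition is unhelpful here.
- **That the Discussion commits the trial to a drug-efficacy claim.** It does say "This study will add to the literature on varenicline and NRT efficacy in PWH", but this is general prose. It specifies no analysis and is not about sex, and the same paragraph opens by describing a test of a delivery approach. It needs no rewriting on this account.

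**Conclusion.** The stated aim of the sex-stratified analyses is wrong as written. They can describe how the effect of PrOMOTE compared with TAU differs by sex; they cannot show what role sex plays in the effect of varenicline. This follows from the article's own text and needs no outside figure.

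The significance condition is a secondary matter of good practice. Its size, 19% to 29% power at 115 per arm, rests on an assumed 20% to 50% women and on an assumed pattern of the full effect in one sex and none in the other. A larger sex difference would be detected more often: with 15% against 49% in men and no effect in women, power is 47% to 69%. The exaggeration of about 1.8 to 2.3 times belongs to the first pattern and a normal approximation.

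The primary results are untouched. At stake is the interpretation of an exploratory finding.

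**What to change.** 1. In Planned analyses, replace the reference to the effect of varenicline with *the effect of PrOMOTE compared with TAU*.
2. As an inexpensive addition, state that the sex-by-arm interaction and the PrOMOTE-against-TAU effect in women and in men will be shown with 95% confidence intervals whatever the interaction p-value, labelled exploratory.

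The first change costs one phrase. The second costs one table of imprecise estimates, which readers must be warned not to over-read. Sex is already a stratification factor, so neither change needs new data, more participants or any alteration to trial conduct.
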